## Abstract

**Background:**

Non-specific low back pain is a common cause for consultation with the general practitioner, generating increased health and social costs. This study will analyse the effectiveness of a multidisciplinary intervention to reduce disability, severity of pain, anxiety and depression, to improve quality of life and to reduce the incidence of chronic low back pain in the working population with non-specific low back pain, compared to usual clinical care.

**Methods/Design:**

A Cluster randomised clinical trial will be conducted in 38 Primary Health Care Centres located in Barcelona, Spain and its surrounding areas. The centres are randomly allocated to the multidisciplinary intervention or to usual clinical care. Patients between 18 and 65 years old (n = 932; 466 per arm) and with a diagnostic of a non-specific sub-acute low back pain are included. Patients in the intervention group are receiving the recommendations of clinical practice guidelines, in addition to a biopsychosocial multidisciplinary intervention consisting of group educational sessions lasting a total of 10 hours. The main outcome is change in the score in the Roland Morris disability questionnaire at three months after onset of pain. Other outcomes are severity of pain, quality of life, duration of current non-specific low back pain episode, work sick leave and duration, Fear Avoidance Beliefs and Goldberg Questionnaires. Outcomes will be assessed at baseline, 3, 6 and 12 months. Analysis will be by intention to treat. The intervention effect will be assessed through the standard error of measurement and the effect-size. Responsiveness of each scale will be evaluated by standardised response mean and receiver-operating characteristic method. Recovery according to the patient will be used as an external criterion. A multilevel regression will be performed on repeated measures. The time until the current episode of low back pain takes to subside will be analysed by Cox regression.

**Discussion:**

We hope to provide evidence of the effectiveness of the proposed biopsychosocial multidisciplinary intervention in avoiding the chronification of low back pain, and to reduce the duration of non-specific low back pain episodes. If the intervention is effective, it could be applied to Primary Health Care Centres.

**Trial Registration:**

ISRCTN21392091

## Background

Low back pain (LBP), in any of its forms (acute, sub-acute or chronic), is a common and important reason for consultation with the general practitioner (GP). The point prevalence rate of LBP has been estimated as 14.8% in a study carried out in the general Spanish population [1], while the same study finds a probability of 44.8% of presenting at least one episode of LBP in a period of six months, similar to the annual prevalence of 41% observed in the Dutch population [2,3].

LBP has an important impact on the performance of daily tasks in individuals who present the condition and on their quality of life. It also has family and social repercussions, which are often ignored [1,3]. It is one of the most frequent causes of absenteeism, estimated at an average of 21.9 days of work sick leave per episode [4]. However, most data related to daily activity come from the field of work and exclude relevant groups such as housewives; thus the consequences of this problem are clearly underestimated [1].

A study carried out in 36 Primary Health Care Centres (PHCC) in Spain describes the management of a patient with non-specific LBP. Courses of action taken include: 98% of the patients receive pharmacological treatment, 19% some kind of physical therapy and 10% are referred to surgery, while 43% of the patients are assessed through radiological techniques. This study showed that, although management of the patients is consistent with the recommendations based on evidence, after two months of treatment, the pain continued in 37% and had worsened in 10% of patients [5].

Multi-causality of LBP limits, in some cases, the election of an approach strategy which improves symptomatology and obtains effective results. Little is known about effectiveness of primary prevention, both in the general population and in the work place. A systematic revision undertaken by Linton et al [6], observed that physical exercise alone showed a weak, though consistent, preventive effect. However, the US Preventive Services Task Force [7] does not find sufficient evidence to support the recommendation for or against postural exercises or modification of risk factors to prevent LBP.

Negative findings obtained in many preventive studies might be explained by various factors. For instance, some studies present methodological defects (small samples, short following-up periods, compliance not always high). Moreover, included populations represent a high variety of occupations, and interventions are too variable in content, frequency and duration [6].

When the problem has already been established, early interventions are necessary to prevent chronicity. Selection procedures of psychosocial risk factors have been used to identify patients with a higher risk of developing long-term disability. In those patients, a cognitive-behavioural interventional approach has proved effective in diminishing that risk [8,9]. Therefore, any LBP approach should consider factors associated with the symptom, which not only can affect the degree of pain, but can increase the risk of it becoming chronic, as in the case of patients with psychological [3,10,11] and/or social aspects.

There is evidence of effectiveness of intensive biopsychosocial multidisciplinary intervention in patients with non-specific chronic LBP, according to a systematic review of randomised controlled trials [12].

A Cochrane review, which assesses the same objective but in sub-acute LBP in adults, only includes two randomised clinical studies which meet criteria for sub-acute LBP (between 4 weeks and 3 months duration), and both studies are classified as being of a low methodological quality. The authors conclude that studies with a high methodological quality are necessary, which include bigger sample size and adequate duration of follow-up to test the objectives[13].

It is generally accepted that LBP becomes chronic when the pain persists for longer than 3 months or occurs episodically within a 6 month period [3,14]. Sub-acute LBP occurs suddenly after a period of at least 6 months without LBP and there is a variability of the duration criteria, which range from 2 to 6 weeks. Research conducted in Spain indicates that after 2 weeks of pain, changes occur in the factors which affect disability and quality of life [15]. The same study associates disability and low quality of life perception with the duration of pain, more than with the degree of pain.

The introduction of clinical practice guidelines in the treatment of LBP [16,17] has incorporated diagnostic aspects, effectiveness of the pharmacological and non-pharmacological resources and patient educational level. However, it may be necessary to integrate other multidisciplinary treatment strategies (physical, psychological and social/occupational) which applied to patients with non-specific sub-acute LBP at the correct time, may avoid chronification of the condition, as well as reduce the individual social and economic impact which this condition has on society.

The main objective is to analyse the effectiveness of a biopsychosocial multidisciplinary intervention approach (rehabilitation or physiotherapy, cognitive-behavioural and pharmacological therapy), to improve disability, reduce pain severity, improve quality of life and reduce incidence of chronic LBP in the working population with non-specific LBP, compared to the usual clinical care.

The secondary objectives are:

- To assess differences between both groups of patients, the group receiving biopsychosocial multidisciplinary intervention and the group receiving usual clinical care, in terms of duration in days of the LBP episode, work sick leave, duration in days of the period of sick leave and pharmacological treatment.

- To assess the responsiveness of the Spanish version of the following questionnaires: Roland Morris disability (RDQ), Mc Gill Pain, Quality of Life (SF-12), Fear Avoidance Beliefs (FAB) and Goldberg questionnaires.

- To compare patient satisfaction with care between both intervention arms.

- To identify factors associated with chronification of a non-specific LBP episode: sociodemographic, clinical (duration of the current episode, severity and others) and psychosocial signs of bad prognosis **(**wrong beliefs, inadequate behaviour, working factors, mood).

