### Study population

Eligible patients will be consecutively selected by their GP, who will inform them about the study objectives. All patients who agree to participate will be given written informed consent to sign.

Patients will be included if the current episode of LBP occurs suddenly after a period of a minimum of 6 months without LBP and lasts between 15 days and 12 weeks [15] and if they do not fulfill any of the exclusion criteria [3].

Furthermore, patients have to be between 18 and 65 years old, and understand Catalan or Spanish and will be accessible for at least twelve months.

Patients will be excluded if: they are unwilling to participate in the multidisciplinary intervention trial; LBP coexists with cognitive impairment or severe psychiatric disorders such as psychosis, or if they have severe major depression; any other cause of disability which impedes answering the various questionnaires; they are pregnant or breast-feeding; they might have anti-inflammatory intolerance or allergy; treatment for physical problems in the preceding three months has been given; and they have been referred for intensive functional restoration programmes or if they have a confirmed diagnosis of fibromyalgia.

Furthermore, the GP has to ensure that the patient has no red flag signs or symptoms that are frequently associated with specific LBP or potentially severe illnesses [5,16,17].

Red flags for possible specific spinal pathology are: oncologic disease during the previous 5 years; constitutional symptoms, unexplained weight loss, fever, chills, recent urinary tract infection; history of drug or alcohol abuse, or immunocompromised host; vertebral fracture (previous history of major trauma: traffic accidents or falls from heights: patients with risk factors of osteoporosis, long term treatment with glucocorticoids); inflammatory spondylarthropathy (SpA) (pain of typical inflammatory night-pattern pain which forces the patient to get up from bed, gradual onset of pain before the age of 40, severe morning stiffness, limited low back mobility on the sagittal/lateral plane, possible inflammatory involvement of peripheral joints, family history, extra-articular manifestations: uveitis, iritis, psoriasis, colitis, urethritis).

Red flags for surgical referral: saddle anaesthesia, recent onset of bladder dysfunction or anal sphincter impairment, major or progressive motor weakness, sensory level, or widespread neurological signs.

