- *Quality of Life measured by SF-12*. We will use the Spanish version of SF-12 because for large group studies, the differences in measurement reliability between the SF-12 and SF-36 are not as important and the SF-12 is worthwhile for specific populations based on large sample sizes [28]. The 12 items provide a representative sampling of the content of the 8 health concepts and operational definitions of those concepts, including what respondents are able to do, how they feel, and how they evaluate their health status. The dimensions were physical function (2 items), physical role (2), social functioning (1), emotional health (2), mental health (2), vitality (1), bodily pain (1), general health (1). The answer options on the Likert scale evaluate the intensity and frequency of these dimensions. Time reference in the version used is 4 weeks. Scores rate from 0 for worse health status to 100 for best health status, for each of the dimensions. The questionnaire should preferably be self-administered.

Secondary outcomes are:

- *Duration of the current episode of LBP (pre-study and study duration)*. We will consider the current episode finished when the pain and its impact on the person's daily life is reduced, even when the pain cannot be cured completely [29].

- *Work sick leave (yes or no)*

- *Duration in days of work sick leave*

- *Percentage of change in pharmacological treatments*.

- *Wrong beliefs, inadequate behaviour and work factors assessed by Fear Avoidance Beliefs Questionnaire (FAB) *[30]. Among psychosocial factors associated with LBP, avoidance behaviour of physical activity or work due to fear of pain have been demonstrated to have an influence on the disability. The Spanish version of the FAB questionnaire allows us to quantify beliefs and fears regarding the causes and consequences of pain, with validity and accuracy in patients with LBP. This questionnaire, recently validated, contains 16 statements (five related to physical activity and eleven to work activity), which patients score from 0 to 6 depending on their degree of agreement or disagreement. Thus, higher scores indicate a higher degree of avoidance behaviour. Completion takes around ten minutes and it can be self-administered.

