### Other variables

The main independent variable is the intervention arm: biopsychosocial multidisciplinary group intervention, or usual clinical care.

The following socio-demographic variables will be recorded: age; sex; educational level (illiterate or non-completed primary studies, completed primary studies, second degree studies, university studies); working situation (housewife, self-employed, employed elsewhere); profession; number of children or other relatives to care for; marital status. Clinical variables: weight and height; previous non-specific acute or sub-acute LBP episodes (none, one or two, three or more); pre-study duration of the current episode of LBP; pain irradiation to the leg (yes or no); severity of pain irradiated to the leg (analogical visual scale); stretching radicular test-Lasegue's maneuver (it has not been carried out, positive if onset of pain irradiated to the leg appears below 30° or between 30-60°, is negative if this pain appears upon 60° or does not appear); prescribed pharmacological treatment: muscle relaxants, analgesics, AINEs, corticoids, ansiolitic drugs, gastric protectors, prescribed diagnostic tests: radiography, Nuclear Magnetic Resonance, Scanner; patient compliance of recommendations and treatments; referrals to other departments (Orthopaedics, Rehabilitation, Neurosurgery, other); Primary Health Care and Hospital emergency visits due to current sub-acute LBP episode; non pharmacological therapeutic measure (relaxation, physiotherapy, reflexology, psychotherapist, etc); vigorous physical activity [33].

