### Data collection and follow-up

All the outcomes will be measured at the individual level. All participants will be invited to attend the PHCC for outcome assessments. They will be assessed on his/her first visit to the PHCC, and at 3 months, 6 months, and 12 months after the onset of LBP. The timing for the second assessment was chosen because it would detect the patients' situation near the point at which they would become chronic. The timing for the last assessment was chosen because adequate follow-up time has been recommended by many authors[6,13]

At each assessment, an expert trained fellow (a psychologist) will make up to three phone calls at different times during the day to make the appointments. During the visit, he/she will fill out the questionnaires by interviewing the participant, will do Lasegue's maneuvre test, will collect information by reviewing medical records, will contact the patient's GP to inquire about their development (compliance of treatment, sick leave, evolution to chronic back pain) and will resolve any questions about the conduct of research.

On January 2009, a pilot study was carried out. Its completion with 14 participants allowed us to: discuss the inclusion and exclusion criteria and the questionnaires used (length, understanding and acceptance): plan the recruitment of patients to achieve a suitable number of participants per group (5 out of 7 invited to participate, attended); redefine the length and distribution of the contents of the intervention and assess adherence to the intervention.

The recruitment period is six months.

Table 4 gives an overview of data collection. Data were entered in a centralised database by the expert trained fellow and the quality of the data will be revised. Figure 1 shows the trial flow chart of the study.

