**Figure 1 F1:**
[figure not shown]
**Study flow chart**. Notes: PHCC = Primary Health Care Centres; GP = General practitioner.

**Table 4 T4:** Overview of data collection

	*Baseline*	*Follow-up*		
**Outcome Measures**	**15 days after onset of LBP**	**3 months**	**6 months**	**12 months**

Disability: Roland Morris Questionnaire (RDQ)	X	X	X	X

McGill Pain Questionnaire	X	X	X	X

Quality of life Questionnaire (SF-12v2)	X	X	X	X

Duration of the current episode LBP	X	X	X	X

Work sick leave (yes or no)	X	X	X	X

Duration of work sick leave in days	X	X	X	X

Percentage of change in pharmacological treatments	X	X	X	X

Fear Avoidance Beliefs Questionnaire (FAB)	X	X		X

Goldberg Scale (Anxiety and Depression) Questionnaire	X	X		X

Satisfaction with care	X	X	X	X

Patients' perceived global assessment	X	X	X	X

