Simple correlations between the scores of the different scales (disability, severity of pain, quality of life and psychosocial scales) will be obtained through the Pearson linear correlation coefficient or the Spearman correlation, in the case of parametric assumptions not being met, at each assessment.

Since the unit of randomisation is the PHCC, we will use a regression analysis of individual level data using methods for clustered data [38]. For adjusting comparisons and to account for cluster randomisation, multilevel linear regression analyses on repeated measures on each of the outcome scales will be used to assess the effect of intervention and to investigate the factors that influence each of the outcome scales at each time point adjusting for baseline scores, baseline characteristics of patients (socio-demographic, clinical and professional) and the other scale scores if they are found to affect outcomes significantly over time. The possible association between intervention and time will be studied. The PHCC and the individual will be considered as random effects and intervention and time as fixed effects.

A multilevel Cox regression model will be used to evaluate the association between the main independent variable, the prognostic factors and the time of subsiding of the current episode of LBP or return to work at 3 months. The patients for whom the duration of the current episode is more than 3 months or those who do not return to work at 3 months will be censored at that time. Kaplan-Meier survival curves will be used to compare the rate of evolution to chronicity and return to work between both groups. Logrank and Breslow test will be used for testing the equality of survival among groups.

The differences in medication prescription at baseline and at each assessment in the interventions and control groups will be compared.

We will calculate the relative risk reduction (RRR) and number needed to treat (NNT) to facilitate development of clinical guidelines for future management.

We will study the interactions and the collinearity. The collinearity of the maximal models will be evaluated using the criteria proposed by Belsley [39]. The significance level of all models will be set at 5%.

The SPSS statistical package for Windows, version 17 (SPSS Inc., Chicago, IL) and the SAS 9.1.3 for Windows (SAS Institute Inc., Cary, NC, USA), will be used for statistical analysis.

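### Episode duration counts time before entry, so pre-study duration can look like a risk factor for chronification even when it does not affect recovery after entry

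*Protocol article*

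**What the plan says.** All references are to the protocol article.

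- **Objective (Background, secondary objectives):** "To identify factors associated with chronification of a non-specific LBP episode: sociodemographic, clinical (duration of the current episode, severity and others"). Psychosocial signs are also listed.
- **Meaning of chronic (Background):** "LBP becomes chronic when the pain persists for longer than 3 months". The same sentence also admits pain that is episodic within 6 months.
- **Outcome (Outcomes, secondary):** "Duration of the current episode of LBP (pre-study and study duration").
- **Predictor (Other variables, and the clinical block of Table 4):** "pre-study duration of the current episode of LBP", recorded at baseline only.
- **Model (Statistical Analysis):** a multilevel Cox regression relates "the main independent variable, the prognostic factors and the time of subsiding of the current episode of LBP or return to work at 3 months". Patients whose current episode exceeds 3 months are censored at that time. Neither the time origin nor the handling of entry time is stated.
- **Entry (Study population):** the current episode "lasts between 15 days and 12 weeks". The baseline column of Table 4 is instead headed "15 days after onset of LBP".
- **Visits (Data collection and follow-up):** follow-up is "at 3 months, 6 months, and 12 months after the onset of LBP".

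**The concern.** The outcome has two additive parts: days from onset to entry, and days from entry to the end of the episode. The first part is also a candidate predictor. Nobody in the study can recover before the day of entry, so pre-study time is immortal time. A patient who enters late has already used up most of the 3 months and has few days left in which to avoid being counted as chronic. An analysis from onset that ignores this gives late entrants a worse outcome even if, from entry onwards, everyone recovers at the same rate.

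The Discussion presents the identification or confirmation of risk factors for chronic low back pain as a strength of the trial. At stake is whether pre-study duration is reported as a prognostic factor when the association comes from how time was counted.

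**Working it through.** **The plan's own figure, and the number analysed.** The protocol gives no figure for this objective, but its sample size reproduces. With a difference of 2.5, SD 5.7, two-sided alpha 0.05 (two-sided assumed) and power 0.90, n = 2 × (5.7 × (1.960 + 1.282) / 2.5)² = 109.2, or 110 per arm. The design effect is 1 + (25 − 1) × 0.1 = 3.4. Then 110 × 3.4 / 0.8 = 467.5, giving 468; without intermediate rounding, 109.24 × 3.4 / 0.8 = 464.3, giving 465. The stated 466 lies between. After 20% dropout, 932 × 0.8 ≈ 746 patients remain for analysis.

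**Time left to recover.** Taking 3 months as day 90, entry at day 15 leaves 75 days and entry at day 84 (12 weeks) leaves 6.

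**Chance of passing day 90 under the null.** Assume a constant recovery rate after entry that does not depend on the entry day d, with median residual episode M. Then P(duration > 90 | d) = 2^(−(90 − d)/M). M is not in the document, so two values are shown.

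| Entry day d | M = 30 days | M = 60 days |
|---|---|---|
| 15 | 2^(−2.5) = 0.18 | 2^(−1.25) = 0.42 |
| 45 | 2^(−1.5) = 0.35 | 2^(−0.75) = 0.59 |
| 75 | 2^(−0.5) = 0.71 | 2^(−0.25) = 0.84 |
| 84 | 2^(−0.2) = 0.87 | 2^(−0.1) = 0.93 |

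Recovery after entry is identical for all of these patients.

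**Null simulation.** 746 patients, M = 30 or 60, 100 replicates per setting, no clustering, tests at 5%. The spread of entry days is an assumption. Cells show the share of replicates in which pre-study duration was significant.

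| Assumed entry days | Logistic, chronic at day 90 | Cox from onset, no delayed entry | Cox with delayed entry, or from enrolment |
|---|---|---|---|
| Uniform 15–84 | 100% | 100% | 2–8% |
| 15 plus exponential (mean 15), capped at 84 | 100% | 100% | 4–6% |
| Uniform 15–30 | 16–27% | 32–80% | 2–6% |
| Uniform 15–21 | 7–10% | 13–26% | 3–7% |
| All at day 15 | predictor does not vary | predictor does not vary | predictor does not vary |

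In the two wide settings the onset-based Cox hazard ratio is 0.35 to 0.46 per 30 days. Per week this is 0.35^(7/30) = 0.78 to 0.46^(7/30) = 0.83. The logistic odds ratio is 2.4 to 3.8 per 30 days. With delayed entry or an enrolment clock, the hazard ratio in those settings is 0.98 to 1.01. With 100 replicates the Monte Carlo standard error at 5% is √(0.05 × 0.95 / 100) ≈ 2.2 percentage points, so 2–8% is compatible with the nominal level.

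A separate simulation took 3 months as day 91, used 200 runs per setting, and drew entry either uniformly over days 15–84 or weighted early (15 plus exponential with mean 20, capped at 84). It gave hazard ratios of 0.79 to 0.83 per week, significant in 100% of runs. Accounting for entry time gave 0.999 to 1.002, significant in 3–5.5% of runs.

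**The case against.** The strongest reply is that the protocol keeps two variables. Other variables and Table 4 record pre-study duration as a baseline predictor, while total duration is listed apart as an outcome. A reader of the objective alone might infer that the same variable stands on both sides and that the analysis is circular. The methods sections do not support that, and the objective's wording is best read as shorthand. What remains is that the outcome contains the predictor as a component.

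Second, the Cox time origin is not stated, and delayed entry is a detail that a full analysis plan could supply. That stands: the artefact is conditional. But the definition of duration, the censoring rule and the candidate predictor are already fixed, and together they point to a clock that starts at onset.

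Third, the size depends on how widely entry days spread. The Study population window and the Table 4 header disagree on this, and under narrow entry the effect is much smaller.

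Fourth, chronicity may not rest on duration alone. Background also counts episodic pain within 6 months, and Data collection and follow-up has the GP asked about evolution to chronic pain.

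Fifth, someone already at day 80 really is more likely to pass 3 months. As prediction the association is true, if trivial. The error would be to read it as an effect on recovery.

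**Conclusion.** The concern holds conditionally, for the risk-factor objective. If the Cox model is timed from onset without delayed entry, or chronic status is a yes/no at 3 months from onset, pre-study duration will appear associated with chronification even when it has no effect on recovery after entry. With entry assumed wide over days 15–84, the null is rejected in about 100% of runs. With entry on days 15–30 it is rejected in 32–80% (Cox) or 16–27% (logistic), and with everyone at day 15 the problem vanishes. These figures assume a constant recovery rate after entry, a median residual episode of 30 or 60 days, and no clustering.

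Three stronger readings are not supported. One is that a strong, significant result is certain whatever the truth: the unstated time origin and the uncertain spread of entry days rule that out. Another is that occupation, beliefs or severity would pick up part of the artefact through correlation with late presentation: this is plausible but was not quantified. The third is that the main trial result is at risk: the arm comparison on the primary disability outcome and the sample size are not affected.

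**What to change.** 1. In the secondary objectives, name the candidate factor as in Other variables: "pre-study duration of the current episode of LBP".
2. In Statistical Analysis, state that patients enter the risk set at enrolment (delayed entry on the time scale from onset), which keeps the 3-month landmark. Alternatively, count time from enrolment.
3. State that any association of pre-study duration with a yes/no chronic status at 3 months from onset will not be interpreted as prognostic.
4. Reconcile the entry window in Study population with the baseline header of Table 4, since the size of the problem depends on it.

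Reading chronic status at an equal interval after baseline from the 6- and 12-month visits would not work directly. Those visits are timed from onset, so the interval since baseline differs by up to 84 − 15 = 69 days between patients.

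The cost is small: some added analysis work and a sentence specifying the time scale. Pre-study duration at baseline and episode duration at each assessment are already in Table 4, so no new data are needed.
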